## Interventions

### Explanation for the choice of comparators {6b}

As already stated, although acne is not an infectious disease, oral antibiotics have remained a mainstay of treatment over the last 40 years. The anti-inflammatory properties of oral antibiotics, particularly cyclines, are effective in treating inflammatory acne [39, 40].

All the guidelines - French [41], European [42] and American [43] - recommend cycline for first-line treatment but limited to a treatment period of 3 months to minimize the development of bacterial resistance. This is why the treatment duration of the comparator arm we chose is doxycycline 100 mg/day for 3 months. The guidelines specify also that monotherapy with a systemic antibiotic is not recommended. Concomitant topical therapy with, for example, benzoyl peroxide should be used with systemic antibiotics and for maintenance after completion of systemic antibiotic therapy. Patients in the two study arms will receive this topical therapy.

The primary objective is the efficacy of doxycycline or spironolactone seen at M4 and/or M6. To avoid results bias and because our experience shows that maximum efficacy is seen for cycline between M4 and M6, the best clinical response between M4 and M6 will be chosen for the primary endpoint.

The response of acne to spironolactone may not be optimal after only 3 months of treatment [22]. A retrospective trial reported by Burcke and Cunliffe showed an average reduction in acne that was optimal at month 6 [24].

In conclusion, in order not to bias the study in either direction, regarding the primary objective, the efficacy of the two treatments will be measured at 4 and 6 months in each arm and the best results in the two arms will be compared (Fig. 1). At the end of the M6 visit, after the clinical evaluation, all the data will be accessible and open to the patient and the investigator. Patients with complete or partial remission will continue the trial. Other patients will drop out of the trial and be treated by the investigators according to their usual practice. The same approach will be used at the M9 visit: relapse patients will drop out of the trial and will be treated by the investigators according to their usual practice.

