### Intervention description {11a}

As this is a double-blind study, the intervention drug, its comparator and the placebo will be managed by the pharmacist of the coordinating centre, CHU Nantes. The oral dose of 150 mg of spironolactone, once a day during the complete trial period has been chosen based on the literature and our own experience. Pills will be dispensed at each protocol visit (i.e. every 2 months for 12 months). The efficacy of spironolactone has been established by several studies that showed improvement, with reductions in lesions ranging from 50 to 100% in women treated for acne [44]. In most of these studies, the dosage range used was 100–200 mg daily, with response noted over approximately 3 months [44].

For the comparator, as recommended by the French Guidelines for acne treatment [41], the doxycycline treatment for acne vulgaris will be 100 mg administered once a day for 3 months. From M4 to M6, a placebo will be administered. Pills will be dispensed at each protocol visit (i.e. every 2 months for 6 months). The two treatments will be taken orally. As the antibiotics must be taken during a meal, and to retain the double-blind effect of our trial, the patients in the two arms should take their treatment during a meal. The treatment should be taken with a full glass of water and the patient should remain in the upright position for at least 1 h.

Monotherapy with a systemic antibiotic is not recommended [43]. Concomitant topical therapy with, for example, benzoyl peroxide 5%, should be used with systemic antibiotics and for maintenance after completion of systemic antibiotic therapy. Patients in the two arms will receive this topical therapy.

The treatment continues after M6, which is the main objective to meet the secondary objectives. However, from the M6 visit, the treatment will be stopped in the event of failure to respond, the patient will be withdrawn from the study and the investigator will prescribe another treatment according to usual practice. In the case of treatment success, the patient in the spironolactone arm will continue with this treatment “open”, and the patient in the doxycycline arm will continue to participate only with the topical therapy*.* The schedule for the complete trial is shown in Fig. 2.

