### Outcomes {12}

The primary endpoint corresponding to the treatment efficacy is determined by the probability of success in each arm. In order to reduce the variability related to the fluctuation over time of the therapeutic response, we took the maximum value of this response. This maximum value appears between the fourth and sixth month of treatment. We could also have taken the average measured over 2 months, but clinically this is not interesting because the optimal time of efficacy is different between the two treatments This probability of success (or relapse) is defined by a decrease in both AFAST scores: (1) AFAST score 1 (corresponding to the GEA score): decrease of at least two grades compared to baseline or to grade 0 if the baseline was at 1, and (2) AFAST score 2 (mandibular score): decrease to grade 1 if baseline was > 1 or to grade 0 if the baseline was at 1.

AFAST score 1 (also called GEA) assesses the comedones (open and closed), the non-inflammatory lesions, the papules and pustules and the nodules. The stage is defined according to a global evaluation of severity of acne and ranges from grade 0 (no acne) to grade 5 (the worst situation). AFAST score 2 assesses acne on an area from the left and right mandibular zone to the upper edge of the trunk and ranges from grade 0 (no acne) to grade 3 (the worst situation).

For the secondary endpoints:
Safety/tolerance: reporting of the number and type of adverse events (AEs) and serious adverse events (SAEs) up to month 12 of follow up and abnormal values of ionogram (sodium, potassium, chlorine and calcium) at 0, 2, 4 and 9 months. First the percentage of AEs and SAEs will be calculated then they will be classified according to the organ affected.Efficacy: these outcomes correspond to the reporting of the:
Number of patients with AFAST score 1 (GEA) at 0 or 1, at M2, M4, M6, M9 and M12Number of patients with AFAST score 2 (mandibular) at 0 or 1, at M2, M4, M6, M9 and M12Number of patients with both AFAST scores 1 and 2 at 0 or 1, at M2, M4, M6, M9 and M12Number of inflammatory lesions of the face at D0 (baseline), M2, M4, M6, M9 and M12Number of retentional lesions of the face at D0, M2, M4, M6, M9 and M12Number of face lesions at D0, M2, M4, M6, M9 and M12Number of trunk lesions (factor F2 of ECLA) at D0, M2, M4, M6, M9 and M12Number of patients with relapses at M4 and M6

The definition of relapse is the same as the primary endpoint:

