### Statistical methods

#### Statistical methods for primary and secondary outcomes {20a}

The primary efficacy variable is the percentage of success defined in “Background and rationale” (paragraph 2.1.2). The comparison between the two arms will be done using a Cochran–Mantel–Haenszel test checking for class of contraception (four strata). Modified intention to treat (ITTm) andlysis will be applied. That implies that to maintain the initial statistical power of the ITTm analysis, all randomized patients will be included in the final analysis, minus those who did not fulfil the inclusion criteria after randomization and those who never began their treatment.

All secondary objectives are expressed as a percentage or a status at a fixed time of follow up. General linear mixed models will be planned to take into account the repeated measurements collected on the same participant during their follow up. The Cox model with time-dependent covariates can also be used for secondary objectives for which a status is considered. Significance will be set at 5% in a bilateral situation.

For the cost-effectiveness analysis, 95% confidence intervals for differential (between arms) costs and QALYs and for the incremental cost-effectiveness ratio (ICER) will be estimated using the non-parametric bootstrap estimation procedure.

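### Safety is compared as a crude percentage to month 12, although exit at M6 and M9 depends on treatment response and reporting is open after M6

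*Protocol article*

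**What the plan says.** Objectives {7} lists clinical and biological safety, followed to 12 months, among the endpoints to be compared between the two arms. Outcomes {12} defines the endpoint as the number and type of adverse events (AEs) and serious adverse events (SAEs) to month 12, together with "abnormal values of ionogram (sodium, potassium, chlorine and calcium) at 0, 2, 4 and 9 months". It gives the summary as "First the percentage of AEs and SAEs will be calculated then they will be classified according to the organ affected". Statistical methods {20a} adds that "All secondary objectives are expressed as a percentage or a status at a fixed time of follow up", and that "The Cox model with time-dependent covariates can also be used for secondary objectives for which a status is considered".

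Four other provisions decide who is observed, and how, after M6:

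- Explanation for the choice of comparators {6b}, on M6: "Patients with complete or partial remission will continue the trial. Other patients will drop out of the trial". On M9: "relapse patients will drop out of the trial and will be treated by the investigators according to their usual practice".
- Intervention description {11a}, from M6: "the treatment will be stopped in the event of failure to respond, the patient will be withdrawn from the study". Responders on spironolactone continue it openly; responders on doxycycline continue with topical therapy alone.
- Trial design {8} and Who will be blinded {17a}: all women are unblinded after M6.
- Methods to handle protocol non-adherence and missing data {20c}: once a woman is released from the study, collection stops, apart from safety data on adverse reactions (ARs): follow-up of ARs, or new ARs associated with the experimental treatment.

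**The concern.** Leaving at M6 means leaving the study, not only the treatment, and it depends on response. The trial is designed on the expectation that response differs between arms. If it does, the doxycycline arm has less time in which an AE can be recorded, and a percentage counted to M12 rises with observation time even when the monthly risk is the same in both arms.

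The same percentage joins two different kinds of data. In the first six months neither patient nor investigator knows the treatment. In the last six, one arm knowingly takes an active systemic drug and the other takes none.

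The Discussion hopes the trial will support prescribing with an acceptable benefit/risk balance. The risk side of that balance should not depend on which arm was watched longer. The primary efficacy analysis is not affected.

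**Working it through.** **Inputs from the article.** Success 70% (spironolactone) and 50% (doxycycline), about 200 women randomised 1:1, from Sample size {14}; exits at M6 and M9 from {6b} and {11a}. The two success rates are the design values: with a two-sided 5% level, 80% power and unpooled variance, n = (1.960 + 0.842)² × (0.70×0.30 + 0.50×0.50) / 0.20² = 90.3, so 91 per group, as the article states.

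**Assumptions.** (a) The share staying after M6 equals the success rate. (b) The AE hazard is constant and equal in both arms for 12 months. (c) Staying does not depend on having had an AE. (d) Women who leave are unobserved from M6.

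**Observation time per 100 women.**
- Spironolactone: 100×6 + 70×6 = 1020 patient-months.
- Doxycycline: 100×6 + 50×6 = 900 patient-months.
- Ratio 1020/900 = 1.13. In months 6-12 alone: 420 v 300.

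**Crude percentage with at least one event by M12.** Let r be the 6-month risk and s the share staying. Everyone faces r once; those event-free at M6 who stay face it again. The crude percentage is r + s·r·(1−r), and the spurious difference is (s₁ − s₂)·r·(1−r). For a monthly hazard h, r = 1 − exp(−6h). Differences below come from unrounded values.

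| Basis for r | r | Spironolactone | Doxycycline | Difference (points) |
|---|---|---|---|---|
| h = 0.02 (assumed) | 11.3% | 18.3% | 16.3% | 2.0 |
| h = 0.05 (assumed) | 25.9% | 39.4% | 35.5% | 3.8 |
| h = 0.10 (assumed) | 45.1% | 62.5% | 57.5% | 5.0 |
| 14.4%, menstrual irregularity in trials, {22} | 14.4% | 23.0% | 20.6% | 2.5 |
| 39.8%, menstrual irregularity in case series, {22} | 39.8% | 56.6% | 51.8% | 4.8 |

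The last two rows treat the {22} figures as 6-month risks. The article gives them no time base, so that is an assumption too.

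**Upper limits.** r(1−r) is largest at r = 50%, where it equals 0.25:
- 70% v 50% staying: 0.20 × 0.25 = 5.0 points.
- 90% v 80%: 0.10 × 0.25 = 2.5 points.
- 80% v 50%: 0.30 × 0.25 = 7.5 points.
- Equal staying: 0.

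**M9 exits.** If, for illustration, 5% of remaining spironolactone women and 20% of remaining doxycycline women also leave at M9, the 70% v 50% case grows from 3.2 to 3.7 points at r = 20%, and from 5.0 to 5.7 at r = 50%.

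**Chance of a false signal.** With 100 women per arm and 70% v 50% staying, the probability of a significant excess on spironolactone at the two-sided 5% level is about 3% to 12% for r from 1% to 70%, against 2.5% nominal.

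**After separation by period.** Over a common six months, or per patient-month, equal hazards give a difference of 0 and a rate ratio of 1.00.

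**The case against.** The strongest reply is that {12} says only that a percentage will be calculated. It gives no denominator, does not say whether women or events are counted, and names no safety test. Splitting tables by period is commonly left to an analysis plan, and the Cox option in {20a} shows that the authors are not confined to crude percentages. This stands in part: the article does not rule out a better analysis. But it does state a between-arm comparison to M12 and a percentage as its measure, and the Cox model is optional and not tied to safety. What is written, if followed, gives the comparison criticised here.

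Second, a reader might take 70% and 50% as the plan's own retention figures. They are not. They are success rates for the best response between M4 and M6 on both AFAST scores, whereas continuation requires full or partial remission at M6. The article gives no retention figure by arm, so the size above is conditional.

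Third, equal constant hazards are unlikely. Doxycycline ends at three months, and after M6 the contrast is active drug against topical therapy alone, so some excess on spironolactone could be real. If first events cluster early, the artefact shrinks. Both points stand. They are also reasons not to merge the two periods, since a merged percentage cannot tell a real excess from extra observation time.

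Fourth, {20c} keeps some safety collection after release. That qualifies assumption (d), but the exception is limited to ARs and does not restore equal AE follow-up. Read literally, its reference to the experimental treatment could make collection less even between arms.

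Fifth, unblinding at M6 is disclosed and justified in {8} and {17a}. A reader might infer that open reporting certainly inflates spironolactone events. The article shows neither the direction nor the size of such an effect.

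Finally, a reader might infer from the ionogram times that a 12-month laboratory safety claim has been made without data. The article makes no such claim; month 9 lies within the 12-month window, and the schedule figure is not shown. What remains is a wording mismatch.

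**Conclusion.** The point holds in a limited form. As written, safety is compared to M12 by a percentage while observation after M6 depends on response, so the two arms are likely to be watched for different lengths of time if the trial's hypothesis is true. Under the 70%/50% proxy and equal constant hazards, the spurious excess on spironolactone is about 2 to 5 points, with 5.0 the ceiling from the M6 exits. It is at most 2.5 points at 90% v 80% staying and nil if staying is equal. For rare SAEs it is small in absolute terms.

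The mixing of blinded and open reporting is a separate weakness that cannot be quantified. The documents do not support saying that the safety result will be biased against spironolactone by a known amount, or that the trial's benefit/risk conclusion would be invalid. The change is worth making because it is cheap and removes the dependence on retention after M6.

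**What to change.** State in the safety analysis that the between-arm comparison is the percentage of treated women with at least one event (AE, and separately SAE) during the blinded 0-6 months. Report months 6-12 separately by arm, labelled open, as events per patient-month under observation, with the number of women remaining.

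Reconcile the 12-month biological safety objective in {7} with the ionogram times in {12}, so that the two sections describe the same period.

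The cost is mainly analysis wording. AEs are already entered in the eCRF in real time ({22}); that event and exit dates can be taken from it is an inference to confirm. The downside is that the formal comparison no longer covers months 6-12, which become descriptive. Losses before M6 could still differ between arms and should be shown.

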### Eligibility criteria {10}

It is commonly acknowledged that acne affecting female patients under 20 years of age is considered to be “adolescent female acne”. Since this protocol concerns adult female acne, the recruited patients will be women aged at least 20 years. These patients will have acne vulgaris with at least 10 inflammatory lesions and no more than 3 nodules. The eligibility criteria are shown in Table 1.

**Table 1 Tab1:** Inclusion and non-inclusion criteria of the FASCE trial

Inclusion criteria	Non-inclusion criteria
• Female patient ≥ 20 years old	• Patient affected by active/progressive diseases, as infections including hidradenitis suppurativa, cancers or endocrine syndrome (e.g. polycystic ovary syndrome)*,* Addison’s disease)
• Patient with acne, with at least 10 inflammatory lesions and no more than 3 nodules (GEA score between 2 and 4)	• Patient affected by rosacea (folliculitis)
• Patient who already had one cycline course for her acne treatment with a 3-month* wash out or who never took any cyclines	• Patient with contra-indication to the use of one of the investigational products or auxiliary: ◦ Patient with intolerance or hypersensitivity to cyclines, spironolactone or to any ingredient present in associated benzoyl peroxide gel ◦ Patient with significant impairment of renal excretory function, acute or chronic renal failure, anuria ◦ Patient with life-threatening or very severe hepatic impairment. (grade III or IV)
• Patient having signed an informed consent	• Patient with hyperkalaemia or strongly requiring potassium-sparing diuretics (e.g. amiloride, canrenoate, eplerenone, triamterene) or treated continuously with ACE inhibitors, angiotensin II antagonist, NSAIDs, heparin and molecular-weight heparin, ciclosporin and tacrolimus, or treated with lithium
• Absence of use of oral antibiotics and zinc salts in the last 30 days	• Patient requiring topical isotretinoin or who stopped this drug less than 2 weeks ago
• Absence of use of topical antibiotics in the last 15 days	• Association with potassium salts except in the case of hypokalaemia
• Absence of use of systemic isotretinoin and antiandrogens in the last 6 months (but antiandrogens used as contraceptive are authorized)	• Patient previously treated with spironolactone
• Absence of microphysiotherapy in the last 15 days	• Pregnant woman or likely to become pregnant or nursing and refusing to use an effective contraceptive method

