### Sample size {14}

For sample size estimation purposes, the targeted difference in the percentage of success is 70% in the experimental arm compared with 50% success in the control arm, indicating a relative increase in success equal to 40%. Assuming a type I error rate of 5% and at least 80% statistical power, the sample size required is at least 91 subjects per group. To take into account the possibility of patients being lost to follow up, 10% (9 subjects) will be added to each group. Finally, approximately 200 subjects will be randomized to the two arms in a 1:1 ratio.

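### The secondary mandibular endpoint (AFAST score 2 at 0 or 1) ignores baseline, so women who start at 0 or 1 reach it without improving and the difference between arms shrinks

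*Protocol article*

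**What the plan says.** Objectives {7} and Outcomes {12} of the protocol article both list the mandibular endpoint as an absolute status: the number or percentage of "patients with AFAST score 2 (mandibular) at 0 or 1, at M2, M4, M6, M9" and M12. Neither refers to the woman's own baseline. The outcomes section adds that percentages will be calculated at each time point.

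The mandibular scale "ranges from grade 0 (no acne) to grade 3 (the worst situation", so a cut-off of 0 or 1 takes in half of its four grades.

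The lesion and severity criterion in Table 1 (Eligibility criteria {10}) is "Patient with acne, with at least 10 inflammatory lesions and no more than 3 nodules (GEA score between 2 and 4". GEA is AFAST score 1, the facial score. No entry criterion mentions score 2.

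Two other rules in the article do look back:

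- The primary success rule reads "AFAST score 2 (mandibular score): decrease to grade 1 if baseline was > 1 or to grade 0 if the baseline was at 1".
- The relapse definition, at the end of the outcomes section, counts a rise of one point in score 2 since the previous visit, in a woman who had been a success, as a relapse.

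**The concern.** A woman can enter the trial with mandibular grade 0 or 1. If she starts at 1 and never changes, she is counted at every visit. If she starts at 0 and worsens to 1, she is counted as well. She cannot come to meet the endpoint through improvement, because she meets it on day 0.

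What is at stake is the one listed efficacy outcome that isolates the mandibular zone. The introduction presents that zone as the reason for using AFAST, on the ground that whole-face scales underrate acne there. If a sizeable share of women start at 0 or 1, the reported percentages will look high in both arms for reasons unrelated to treatment, and a real difference among women with mandibular disease will look smaller than it is.

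**Working it through.** **1. The rules side by side, for score 2 only**

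| Baseline to visit | Secondary endpoint (0 or 1) | Mandibular part of primary rule |
|---|---|---|
| 2 or 3 to 1 | reached | met |
| 1 to 1 | reached | not met (must reach 0) |
| 1 to 0 | reached | met |
| 0 to 1 | reached | no decrease; baseline 0 is not covered |

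The relapse rule adds a further clash. A woman who is a success at M4 with mandibular grade 0 and is at grade 1 at M6 is a relapse at M6, yet still counts as 0 or 1 at that visit.

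**2. The plan's own figure**

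Sample size {14} assumes "70% in the experimental arm compared with 50% success in the control arm". With a two-sided 5% level and 80% power, the unpooled formula gives (1.960 + 0.842)² × (0.50×0.50 + 0.70×0.30) / 0.20² = 7.85 × 0.46 / 0.04 = 90.3, so 91 per group, as stated. The pooled-variance version gives 93. This figure concerns the primary endpoint; the article makes no power claim for the mandibular endpoint.

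**3. Dilution**

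Let f be the share starting at mandibular 0 or 1, s the share of those still at 0 or 1 at the visit, and p the response rate in women starting at 2 or 3.

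Observed rate = f×s + (1−f)×p. With s equal in both arms, the observed difference is (1−f) × (p_E − p_C).

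Inputs: p = 70% and 50% are borrowed from the primary endpoint as an illustration. f = 20, 40, 60% and s = 95% are assumptions. 100 per arm follows from about 200 women randomised 1:1.

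For f = 20%: 0.20×0.95 + 0.80×0.70 = 0.75 and 0.20×0.95 + 0.80×0.50 = 0.59, a difference of 16 points.

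Power = Φ[(d − 1.96×√(2p̄(1−p̄)/n)) / √((p_E(1−p_E) + p_C(1−p_C))/n)], with p̄ the mean of the two rates. The restricted analysis uses n = 100(1−f) per arm and 70 v 50%.

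| f | All women: rates | Difference | Power, all women | Power, baseline above 1 only |
|---|---|---|---|---|
| 0 | 70 v 50% | 20 | 83% | 83% |
| 20% | 75 v 59% | 16 | 67% | 74% |
| 40% | 80 v 68% | 12 | 49% | 61% |
| 60% | 85 v 77% | 8 | 30% | 45% |

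If every low-start woman stays at 0 or 1 (s = 100%), all-women power is 68, 51 and 34%. With 91 per arm and s = 95% it is 63, 45 and 28%. The pattern does not depend on the exact choice.

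**4. If treatment also affects the low-start women**

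With different staying rates, the difference is (1−f)×20 + f×(s_E − s_C). It returns to 20 points only if s_E − s_C is itself 20 points, for example 100 v 80%. A smaller difference in staying leaves some dilution.

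**The case against.** The strongest reply is that the article does not call this outcome a success or a response. It reports a status at a fixed time, and comparing a status between randomised arms is valid: low-start women are expected equally in both arms, so neither drug gains. That stands, and it limits the point to sensitivity and interpretation.

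The primary endpoint already requires a baseline-referenced mandibular decrease, so the trial does not rest on this outcome for its mandibular evidence. That also stands. But the primary endpoint combines two scores and cannot show the mandibular effect alone.

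The inputs to the illustration are assumed, and the 70 v 50% describes a best response between M4 and M6 on both scores. That is correct: the table shows direction and possible range, not an estimate. The SAP may specify a baseline-adjusted model, which could recover some precision, but it would not change who is counted in the percentages.

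A reader might go further and infer that the outcome requiring both scores at 0 or 1 suffers the same inflation and dilution. The documents do not support that. Entry requires GEA 2 to 4, so every woman counted there has improved by at least one GEA grade, and there are no automatic successes.

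A reader might also infer that this both-scores outcome is the complete remission listed in Objectives {7}. The two stand in matching list positions, but the article never labels one as the other. The comparator section says "Patients with complete or partial remission will continue the trial", which separates two states without defining either. The definition may sit in the full protocol.

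**Conclusion.** The point holds for the mandibular endpoint alone. As written, it counts women who have not improved, and some who have worsened, and it disagrees with the primary and relapse rules on the same scale. It raises both arms' rates, provided low-start women stay at 0 or 1 more often than the others get there, and it shrinks the absolute difference by the factor 1−f when staying rates are equal. Under the assumed 20, 40 and 60%, a 20-point effect is seen as 16, 12 and 8 points, and the comparison restricted to women above grade 1 has more power despite fewer women. The true size cannot be stated, because the baseline mandibular distribution is not given.

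This is a secondary endpoint. The primary endpoint and the 91 per group are untouched, and no bias towards either arm is shown.

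On complete remission only a conditional remark is justified. If the both-scores outcome is meant to be that objective, the name overstates it: the GEA scale "ranges from grade 0 (no acne) to grade 5 (the worst situation", the mandibular scale likewise reserves no acne for grade 0, and grade 1 on either is above that.

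**What to change.** Make the between-arm comparison of mandibular score 0 or 1 in women whose baseline score 2 is above 1. In women who start at 0 or 1, report worsening separately. Keep the all-patient percentage at each visit as description.

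If the both-scores outcome is intended as the complete remission objective, label it as scores of 0 or 1 on both scales; if complete remission is defined otherwise in the full protocol, the outcome list should say so.

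The cost is wording in the endpoint list and the SAP. Baseline score 2 is already needed for the primary rule, so nothing new is collected. The subset is defined by a baseline value, so the comparison within it remains randomised. The downside is a smaller set: 80, 60 or 40 women per arm out of 100 under the shares assumed above. Low-start women also leave the between-arm test, so any protective effect in them appears only in the separate report on worsening.

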### Trial design {8}

Our study is a randomized double-blind trial for the first 6 months (timeline for primary objective), and is an open trial for the last 6 months of follow up. The female patients will be randomized either to the acne routine-care arm, i.e. cycline (doxycycline 100 mg/day for 3 months followed by a placebo for 3 months) or to the experimental drug arm (spironolactone 150 mg/day for 12 months).

Blinding will be removed for all patients after 6 months of evaluation - once the primary endpoint has been measured - whatever the result, to limit the constraints for the patients in the doxycycline arm. If blinding were maintained, patients in the doxycycline arm would have to take a placebo for up to 6 months in addition to the 3 months already taken. The objective of the last 6 months of follow up is to assess the maintenance of each treatment’s efficacy during this time.

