AFAST score 1 (GEA score): increase of 2 points in the score at the previous visit, in the case of success, orAFAST score 2 (mandibular score): increase of 1 point in the score at the previous visit, in the case of success
Number of patients with reappearance of 10% or more of inflammatory lesions at M6

For these nine outcomes, percentages will be calculated at each time point:
Quality of life (QoL): reporting of the scores of two QoL questionnaires: the Euroqol-5 dimensions (EQ-5D) and the Cardiff Acne Disability Index (CADI) at M2, M4, M6, M9 and M12. This outcome will be measured by the percentage of patients whose quality of life has improved relative to baseline.Microflora: bacterial and parasitic sampling at D0 and M4. The presence *of P. acnes, M. Furfur* and *S. epidermidis/ aureus* will be sought and a change in these populations from baseline will be measured at M4. A percentage of decrease will be calculated.Medico-economy: incremental cost-effectiveness ratio (cost per quality-adjusted life year (QALY)) of the comparison between spironolactone and cycline at 6 months. Criteria for the calculation of the cost-effectiveness ratio are detailed in “Methods for additional analyses”.

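### The relapse endpoint is said to match the primary endpoint but does not: it can overlap with success, can miss a stepwise facial return to baseline, and is not reported after M6

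*Protocol article*

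**What the plan says.** All statements are in the protocol article.

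- **Success (Outcomes {12}).** Both AFAST components must improve against baseline. Face score (AFAST score 1, GEA): "decrease of at least two grades compared to baseline or to grade 0 if the baseline was at 1". Mandibular score (AFAST score 2): "decrease to grade 1 if baseline was > 1 or to grade 0 if the baseline was at 1".
- **Relapse (Outcomes {12}).** The list is introduced by the sentence "The definition of relapse is the same as the primary endpoint". The rules that follow are, for the face score, "increase of 2 points in the score at the previous visit, in the case of success", or, for the mandibular score, "increase of 1 point in the score at the previous visit, in the case of success".
- **When relapse is counted.** Objectives {7} and Outcomes {12} agree on M4 and M6 only.
- **Aim of the second half-year (Trial design {8}, repeated in {17a}).** "The objective of the last 6 months of follow up is to assess the maintenance of each" treatment's efficacy.
- **Use of relapse after M6 (Explanation for the choice of comparators {6b}).** Women who have relapsed at M9 leave the trial. No relapse outcome is listed at M9 or M12.

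**The concern.** The sentence that equates the two definitions cannot be true of the rules printed beneath it. The reference differs (baseline against previous visit), and so does the way the components combine (both against either). An analyst cannot follow both statements.

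Three consequences need checking: whether one visit can count as success and as relapse; whether a woman can return to her baseline face grade without being counted; and whether the period set aside for maintenance has a relapse measure. At stake is the meaning of the between-arm comparison of relapse percentages, which is a listed secondary objective.

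**Working it through.** **Planned figure.** The article gives no expected relapse rate, so there is none to reproduce. The sample size of 91 per group rests on the primary endpoint and does not depend on this point.

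**Inputs.** Eligible baseline: "GEA score between 2 and 4" (Eligibility criteria {10}). The face score runs from 0 to 5 and the mandibular score from 0 to 3 (Outcomes {12}). Success and relapse rules are as quoted.

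**Reading assumptions.** Increases mean at least 2 and at least 1 point. A fall to mandibular grade 1 means grade 1 or lower. A mandibular baseline of 0, which the success rule does not cover, is taken as needing to stay at 0.

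**Step 1. Transitions from a success visit.**
- GEA grades that count as success: 1, 2 and 3 grades for baselines 2, 3 and 4, in total 6.
- Mandibular grades that count as success: 1, 1, 2 and 2 grades for baselines 0, 1, 2 and 3, in total 6.
- Starting states: 6 × 6 = 36. Possible next states: 6 × 4 = 24. Transitions: 36 × 24 = 864.

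**Step 2. Relapse while still a success.**
- Mandibular 0 to 1 with baseline 2 or 3, GEA staying within success: (1² + 2² + 3²) × 2 = 28.
- GEA 0 to 2 with baseline 4, no mandibular rise: 1 + 1 + 3 + 3 = 8.
- Total: 28 + 8 = 36 of 864.

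Example: baseline GEA 3, mandibular 2; previous visit (1, 0), now (1, 1). The mandibular point makes this a relapse, yet GEA is still two grades below baseline and mandibular grade 1 still qualifies. Second example: baseline GEA 4, mandibular 1; (0, 0) then (2, 0). GEA has risen by two and is still two below baseline.

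**Step 3. Success lost without a relapse call.** This needs a one-grade GEA rise out of success with no mandibular rise: (1 + 1 + 3 + 3) = 8 for each of three GEA baselines, so 24 of 864.

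**Step 4. Stepwise return to the baseline face grade at M2, M4, M6.**

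| Baseline GEA | M2 (success) | M4 | M6 | Largest step |
|---|---|---|---|---|
| 2 | 0 | 1 | 2 | +1 |
| 3 | 1 | 2 | 3 | +1 |
| 4 | 2 | 3 | 4 | +1 |

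No step reaches +2, so the face rule never fires. The mandibular rule does not fire either as long as that score does not rise. The number of non-rising mandibular sequences is 1, 1, 4 and 4 for baselines 0 to 3, so 10 × 3 = 30 such paths. This count does not enforce the condition that the previous visit was a success. Enforcing it could only add missed paths, because after M4 the woman is no longer a success.

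**Step 5. Time points.** Relapse is counted at M4 and M6, acted on at M9, and reported at neither M9 nor M12.

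All counts are of possible score paths. They are not frequencies of patients.

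**The case against.** **Relapse and success answer different questions.** A woman can worsen from a response already gained and still be better than at baseline, and no listed analysis needs the two states to exclude each other. That is a defensible concept, but it is not the one the article states, since it says the definitions are the same. The overlap is also confined to the baselines in Step 2.

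**The wording is ambiguous.** The previous visit may mean the last visit at which success was present. Then 1, 2, 3 is a two-point rise from the success score and is caught at M6. This stands: the missed return in Step 4 depends on the literal reading. The overlap in Step 2 does not, since it arises in a single step from a success visit.

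**Other measures exist.** This also stands. A reader might infer that slow relapse is invisible or that M9 and M12 contribute nothing. The documents do not support either. The mandibular rule catches any one-grade rise from success, a lesion-based recurrence outcome is listed at M6, and seven AFAST and lesion-count outcomes, plus quality of life, run to M12. The gap is in the GEA part of the relapse rule and in the relapse outcome itself.

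**M4 and M6 fall in the blinded period.** Limiting a comparative endpoint to blinded visits is reasonable. It still leaves relapses found at M9 removing women from follow-up without entering any relapse outcome.

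**Bias between arms.** A reader might infer that the rule favours doxycycline, because that arm moves to placebo after 3 months and might relapse gradually. No passage says that relapse after doxycycline is slow, and section {6b} places maximum cycline efficacy between M4 and M6. The design allows a difference between arms; the documents give neither its size nor its direction.

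**Conclusion.** The point holds as a defect in the definition of one secondary endpoint. The contradiction between the stated equivalence and the printed rules is plain on the page, as is the overlap of success and relapse (36 of 864 possible transitions, at specific baselines). The missed stepwise return can occur at every eligible baseline GEA, but only on the literal reading of the reference visit and only when the mandibular score does not rise. The absence of a relapse outcome at M9 and M12 is a mismatch with the stated aim of months 6 to 12, partly offset by the other outcomes measured to M12.

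The primary endpoint, its test and the sample size are not touched. How many women would be affected cannot be derived from the article. The conclusion rests on the reading assumptions listed with the calculation.

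**What to change.** - **Definition.** For the endpoint, call a woman relapsed when she no longer meets the success definition in Outcomes {12} (both components, against baseline) at a visit after one at which she met it. This removes the overlap and counts the stepwise return.
- **Time points.** Report at M4 and M6 as blinded results, and at M9 and M12 as a labelled open-label analysis.
- **Comparison.** Compare arms on success achieved and still present, with all modified-intention-to-treat women as denominator. Count women withdrawn for non-response or relapse as not in maintained success. This endpoint then needs a stated exception to section {20c}, which drops women with missing data from the clinical secondary analyses.
- **Consistency.** Reconcile the relapse wording in {6b} and {12}. Clinical management of women who relapse stays with the investigators.

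**Cost.** Wording of one endpoint, using AFAST scores already scheduled at these visits. Relapse rates would no longer be on the planned scale. M9 and M12 scores will be absent for women already withdrawn, since {20c} collects only safety data after release; for those withdrawn for non-response or relapse, the counting rule above supplies their status without a score.
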